#### Study 2—Cambridge Colour Test

For the Trivector subtest of the CCT, we will use a one-way MANOVA, with three dependent variables (thresholds for protan, deutan, and tritan; continuous variables), and one independent, within-subject variable (condition ∼ three levels). For the Ellipse subtest, we will conduct a separate MANOVA for Ellipse 1 with two dependent variables (angle and area; continuous variables) and one independent, within-subject variable (condition ∼ three dosage). A moderation or mediation analysis (using 5,000 bootstrapping resamples) will be conducted to determine whether the area, length, angle, or ratio is a better predictor of any results of the CCT.

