#### Study 2—Cambridge Colour Test

The primary aims of this second study period are investigating whether any of three conditions (placebo, 2-mg, or 4-mg doses) (a) influence chromatic contrast discrimination for the S-, M-, and L-wavelength sensitive cones (blue, green, and red, respectively) using the Trivector subtest; (b) influence the position and direction (e.g., larger or more circular ellipses indicate worse discrimination) of an MacAdam chromatic discrimination ellipse for on an achromatic background (Ellipse 1); (c) determine whether there is a dose effect; (d) determine whether there is an interaction between the dosages and direction of the chromatic contrast discrimination; (e) are the results related to BMIs; (f) are different with regard to sex; and (g) determine whether there is an interaction between cotinine concentration and chromatic contrast discrimination. Exploratory aims will test effects by age, height, weight, and years of education.

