### Sample Size

There were no previous reports of sample size estimation from a meta-analysis or equivalent study. Because of the lack of this information, the effect size will be estimated using the minimal meaningful effect size (0.05) (Sullivan and Feinn, 2012) and the power will be used considering a common value in clinical trials (Charan and Biswas, 2013). Considering a two-sided test with an alpha value of 0.01 (or 0.02 for a one-sided test) and a power of 85% (or 0.85), the sample size would require at least 42 individuals to complete the three periods for each study. As this trial is a single group model, with an anticipated 20% attrition rate, our main intention is to enroll 50 individuals for each study (Study 1, *N* = 50; Study 2, *N* = 50). Although our sample size is larger than that of previous studies using these tests (Andrade et al., 2019; Fernandes et al., 2019a,b), it is important to provide an estimation that covers our outcomes (e.g., BMIs and cotinine).

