### Outcome Measures

The primary outcomes of this study are about the effects of nicotine on achromatic contrast sensitivity at the various spatial frequencies (Study 1) and on chromatic contrast discrimination using the Trivector threshold values and the various elliptical parameters like angle of the major axis, major axis length, axis ratio, and area (Study 2). For Study 1, the higher the curve, the better the discrimination ability. For Study 2, the area of the ellipse is a general index of chromatic discrimination. That is, the smaller the ellipse, the better the discrimination ability. Provided that there is a statistically significant main effect or interaction, results will be related to the statistical analysis: an improvement of 10% will be considered as meaningful difference for each spatial frequency (Study 1) and for each parameter of the CCT (Study 2). The primary outcome will be assessed after the three sessions are completed. As previously noted, we did not observe learning or practical effects when using Metropsis software (Fernandes et al., 2019a) and the CCT (Fernandes et al., 2020). The secondary outcomes are related to demographic data (effects of age, years of education, height, and weight), BMI, and gender effects. Serum cotinine levels (ng/ml) after each session (placebo, 2 mg, and 4 mg of nicotine gum) will be used as predictors of response (for each visual test) in a multivariate regression analysis. Data will be double-checked and stored at an open access repository (figShare; available upon request).

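### Study 2 ellipse analysis leaves shape untested, treats the major-axis angle as an ordinary number, and applies a 10% improvement rule that is undefined for angle

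*Protocol article*

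**What the plan says.** Outcome Measures places among the Study 2 primary outcomes the Trivector thresholds and the "various elliptical parameters like angle of the major axis, major axis length, axis ratio, and area". It then sets one rule for relevance, conditional on a significant main effect or interaction: "an improvement of 10% will be considered as meaningful difference for each spatial frequency (Study 1) and for each parameter of the CCT".

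The Study 2 part of Statistical Analysis gives the ellipse test of condition: "we will conduct a separate MANOVA for Ellipse 1 with two dependent variables (angle and area; continuous variables". Condition is the within-subject factor with three levels. Length and ratio appear only in the next sentence, where a moderation or mediation analysis with 5,000 bootstrap resamples is meant "to determine whether the area, length, angle, or ratio is a better predictor of any results of the CCT".

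The direction of benefit is given for size in Outcome Measures ("the smaller the ellipse, the better the discrimination ability") and for size and shape in item (b) of the Study 2 aims ("larger or more circular ellipses indicate worse discrimination"). No direction is given for angle, nor any range, origin or axial method for it.

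**The concern.** Four points arise from these passages.

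1. **Outcomes against tests.** Four ellipse parameters are named and two are tested. Shape, which the aims treat as a sign of worse discrimination, is not among the two.
2. **Scale of angle.** A major axis has no head or tail, so its angle repeats every 180 degrees. Analysed as a plain continuous variable, two nearly identical axes on either side of the wrap point look far apart. That can distort means and hide or create a condition effect.
3. **The 10% rule.** It is extended to each CCT parameter, and angle is one of the listed parameters.
4. **The moderation/mediation step.** Ellipse parameters are asked to predict unspecified CCT results, of which they are themselves a part.

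At stake is whether the ellipse result can be read against the declared primary outcomes, and whether half of the bivariate test rests on a variable whose mean depends on an arbitrary zero.

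**Working it through.** The plan gives no figure specific to the ellipse analysis, so there is none to reproduce. The 42 completers from Sample Size serve below only as the number of subjects.

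**1. Listed against tested.** Listed: angle, length, ratio, area (4). Tested for condition: angle, area (2). With L the full major axis and ratio = major/minor, the minor axis is L/ratio, so

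area = π × (L/2) × (L/(2 × ratio)) = π × L² / (4 × ratio).

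On the log scale, log area = constant + 2 log L − log ratio. Regressing simulated log area on log length and log ratio gave coefficients 2 and −1 with no residual. The three size and shape parameters therefore carry two independent dimensions. Area is tested, so one dimension remains untested. Putting log area, log length and log ratio into one MANOVA would not work, because they are exactly collinear.

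**2. Angle: the wrap.** Axes at 2 and 178 degrees differ by 4 degrees. Their arithmetic mean is (2 + 178)/2 = 90; their axial mean is 0 (equivalently 180).

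**3. Angle: effect on a paired test.** Assumptions: 42 subjects, two conditions, two-sided alpha 0.05, between-subject SD as shown, within-condition noise SD/2, true rotation SD/2, angles recorded on 0 to 180 degrees, 1,500 replicates. The linear test uses raw differences; the axial test wraps each difference to ±90 degrees.

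| Centre | SD | Power, linear | Power, axial |
|---|---|---|---|
| 0 | 20 | 0.41 | 1.00 |
| 45 | 20 | 0.52 | 1.00 |
| 90 | 10 | 1.00 | 1.00 |
| 90 | 20 | 0.98 | 0.99 |
| 90 | 30 | 0.79 | 0.99 |

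The loss depends on how near the axes lie to the wrap point and how widely they spread.

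**4. Angle: precision of the fitted axis.** The eight vectors come from the Study 2 stimulus section. The 15% lognormal threshold noise, the axis ratios and the true angle of 60 degrees are assumptions. Over 3,000 fits per setting, the axial SD of the fitted angle was about 30, 13 and 7 degrees at ratios 1.2, 1.5 and 2.0. The linear mean was 66 at ratio 1.2, but 59.9 and 59.6 at ratios 1.5 and 2.0. With a true angle of 90 it was 90.7 even at ratio 1.2. With a true angle of 5 it was about 50 even at ratio 2.0.

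**5. Dilution.** Take a Hotelling-type test with 42 subjects and three conditions, so two contrasts per variable. Suppose area alone (2 numerator degrees of freedom) gives 85% power. Adding an angle that is independent of area and carries no effect raises these to 4. Power falls to 74% at alpha 0.05 and to 72% at alpha 0.01.

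**6. The 10% rule.** Ten per cent of an angle is 1 degree at 10 degrees and 17 degrees at 170 degrees. These two axes are only 20 degrees apart, and the difference in tolerance comes purely from where zero is placed. With no better direction, an improvement cannot be defined either.

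**7. The moderation/mediation step.** If the outcome is an ellipse parameter, the identity in step 1 produces an association by algebra. If it is a Trivector threshold, which comes from a separate subtest with its own staircases, it does not. The sentence does not say which, and it names no mediator or moderator.

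**The case against.** The strongest reply has five parts.

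- **The list is illustrative.** Outcome Measures introduces the parameters with a word that signals examples, and length and ratio do appear in the analysis section. A reader might infer that two primary outcomes are simply abandoned. The identity does not support that count: given area, only shape is missing. That one gap stands, because the analysis section names its dependent variables and ratio is not one of them.
- **MANOVA can cope with angle.** A reader might conclude that it cannot. The documents do not show this. With axes clustered well away from the wrap point, linear and axial tests perform almost alike. Angle coding could also sit in a fuller protocol or SAP. What stands is that the article calls angle continuous and states nothing that protects against the wrap.
- **The noise figures are assumed.** This is correct. The 30-degree SD belongs to the most circular ellipse tried and falls to 7 degrees at ratio 2.0. The dilution arises only if angle carries no effect.
- **The moderation/mediation step need not be circular.** This is also correct if Trivector thresholds are the outcome. The criticism that holds in every reading is that no outcome is named.
- **Angle belongs in the study.** Items (b) and (d) of the Study 2 aims ask about direction, and angle is the ellipse parameter that expresses it. A case for demoting or removing angle would therefore contradict a stated aim.

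No part of this reply rescues the 10% rule for angle.

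**Conclusion.** The point holds in a limited form. Two parts are firm and need no assumptions: shape has no test of condition although it is covered by the primary outcomes and given a meaning in the aims, and the 10% rule cannot be applied to angle. One part is conditional: raw-angle analysis is unsafe if axes lie near the wrap point or spread widely (power 0.41 against 1.00 in one assumed setting), and nearly harmless if they cluster away from it (0.98 against 0.99 in another). The documents give no angle distribution, so they do not settle which applies. The moderation/mediation step is underspecified, and circular only where ellipse parameters predict ellipse results. The point does not show that MANOVA must fail here or that angle should lose its place among the outcomes. The change should be made before the data are unblinded, but it does not threaten the trial's design.

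**What to change.** In Outcome Measures and the Study 2 part of Statistical Analysis:

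1. Test condition on log area and log axis ratio in one within-subject MANOVA. State that length follows from these two and gets no separate test.
2. Keep angle, since it serves the aim on direction, but analyse it as the pair cos(2 × angle), sin(2 × angle) in a separate test, so that it does not dilute the area and ratio test.
3. Limit the 10% rule in Study 2 to the Trivector thresholds and area, with lower stated as better for both.
4. Limit the moderation/mediation analysis to named outcomes not computed from the ellipse, such as the Trivector thresholds, and name the mediator or moderator; otherwise drop it.

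No new data or visits are needed. The cost is wording, slightly more analysis work and one further test to account for. The area and ratio MANOVA still has two dependent variables, so it has the same numerator degrees of freedom as the present one.

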#### Additional Analyses

Missing data will be considered as random (MAR), and the maximum likelihood estimation (MLE) will be used. Under the MAR assumption, MLE appears to represent an interesting and unbiased approach, even to continuous and discrete variables (Dziura et al., 2013). Nevertheless, we will analyze individuals with missing data and without missing data. We expect to have no more than 5% of missing data and differences between with and without missing data.

Exploratory analysis to investigate whether sex, age, and level of education are predictors of response will be performed. Multivariate regression analysis will be used to investigate whether demographics would be predictors of the effects of nicotine gum. We will also conduct a separate regression analysis to investigate whether or not cotinine serum levels would be predictors of visual performance. These variables can be also used as mediators of the interaction between conditions.

Finally, adverse events will be presented as percentages in each condition. Cochran’s *Q* test will be conducted to investigate the effectiveness of the masking and blinding (on this analysis, we will calculate the ratio between errors and correct responses regarding the condition in which the participant believed was applied).

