#### Study 1—Contrast Sensitivity Function

For the contrast sensitivity analysis, we will use a multivariate analysis of variance (MANOVA), with eight dependent variables (thresholds of each spatial frequency; continuous variables) and one independent, within-subject variable (condition ∼ three levels). *Post hoc* testing will be conducted using discriminant analysis.

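### Missing data are to be handled by maximum likelihood, but the primary MANOVAs in their standard form use complete records only, and the article does not say how the two connect

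*Protocol article*

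**What the plan says.** For Study 1, the Statistical Analysis section says "we will use a multivariate analysis of variance (MANOVA), with eight dependent variables", one per spatial frequency, with condition (placebo, 2 mg, 4 mg) as a three-level within-subject factor. For the Trivector test in Study 2 it says "we will use a one-way MANOVA, with three dependent variables" and the same within-subject factor. A separate MANOVA with two dependent variables, angle and area, covers Ellipse 1. The software is SPSS 25.0 and MATLAB.

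Additional Analyses then says "Missing data will be considered as random (MAR), and the maximum likelihood estimation (MLE) will be used". It adds "Nevertheless, we will analyze individuals with missing data and without missing data" and "We expect to have no more than 5% of missing data". It does not say which analysis the maximum likelihood step belongs to, or whether the 5% counts values, sessions or participants.

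The Sample Size section requires 42 people per study to finish all three periods, anticipates 20% attrition and enrols 50 per study. The section on safety, dropouts and adherence counts as a dropout anyone who misses two visits in a row, does not complete every gum administration, has a severe adverse event or withdraws.

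**The concern.** A repeated-measures MANOVA laid out with one row per person needs every entry in that row. It has no step that draws on a partly filled row; the person is dropped. Maximum likelihood under MAR does the opposite: it uses whatever each person contributed. The article commits to both and gives no bridge.

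Two things are at stake. The first is the assumption. A complete-case result generally needs missingness to be unrelated even to the observed outcomes, which is stronger than the MAR assumption stated. Severe adverse events are a listed reason for dropout and nausea and headache are listed nicotine effects, so loss related to condition or response is plausible. The second is information. Someone who completes two sessions and then leaves has given a usable within-person comparison, and listwise deletion throws it away.

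Left open, the choice of who counts in the primary result would be made after the data are seen.

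**Working it through.** **Values needed per person** (dependent variables × 3 conditions, from the Statistical Analysis section)
- Study 1: 8 × 3 = 24
- Trivector: 3 × 3 = 9
- Ellipse 1: 2 × 3 = 6

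**The plan's own target.** The 42 completers could not be reproduced from the stated inputs alone. The figure appears if the effect size of 0.05 is read as partial eta-squared, with alpha 0.01, power 0.85 and a correlation between sessions of about 0.6; neither that metric nor that correlation is stated. Here 42 is simply taken as the plan's requirement. Fifty enrolled with 20% attrition gives 50 × 0.80 = 40 complete people, 2 short of 42; covering 20% would need 42 / 0.80 = 52.5, so 53. That shortfall is a separate point. It matters here because a complete-record analysis takes the whole loss and also drops the sessions those 10 people had already recorded.

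**Complete records at the stated 5%, starting from 50.** With missing rate q over k required units, lost independently, the expected number complete is 50 × (1 − q)^k.

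| What the 5% counts | Calculation | Complete of 50 |
|---|---|---|
| Participants | 50 × 0.95 | 47.5 |
| Sessions (k = 3) | 50 × 0.95^3 | 42.9 |
| Single values, Ellipse 1 (k = 6) | 50 × 0.95^6 | 36.8 |
| Single values, Trivector (k = 9) | 50 × 0.95^9 | 31.5 |
| Single values, Study 1 (k = 24) | 50 × 0.95^24 | 14.6 |

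At lower rates of independent single-value loss, Study 1 keeps 50 × 0.99^24 = 39.3 at 1% and 50 × 0.98^24 = 30.8 at 2%.

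**Precision under the single-value assumption.** For a comparison of two conditions at one frequency, the standard error with complete cases relative to all available pairs is √[(1 − q)^2 / (1 − q)^24]. This is 1.12 at 1%, 1.25 at 2% and 1.76 at 5%.

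**Routes by which maximum likelihood could enter**
- EM fill-in, then MANOVA. Incomplete people are retained, but the filled values are analysed as if observed, so the error is understated.
- One row per session. A missing value costs a session and not the person, but the pairing is ignored, which contradicts the within-subject factor.
- A likelihood-based repeated-measures model. This delivers what Additional Analyses describes, but it is not the MANOVA named for the primary analysis.

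**The case against.** The strongest reply is that the article never restricts the MANOVAs to complete participants. It says maximum likelihood will be used and that "we will analyze individuals with missing data and without missing data", so the intent is plainly to include incomplete people, and the mechanics may sit in a full protocol or analysis plan that is not shown. This stands in part. A reader might infer that the primary result is fixed as complete-case and that maximum likelihood can never reach it. The text does not support that, because an EM step would bring it in, though with understated error. What remains is a mismatch between two choices that the article itself makes, not a missing detail.

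A reader might also take the sentence just quoted as promising a MANOVA of incomplete people alone, which could not be run. The more natural reading is two runs, one including and one excluding them, since the article goes on to speak of differences between the two. That is an ordinary sensitivity analysis.

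Finally, a reader might take 15 of 50 as the expected outcome in Study 1. It needs every threshold to go missing independently. The dropout definition points to loss of whole sessions or people, and an aborted session would probably lose several frequencies together. Loss of isolated thresholds is conceivable, since the article plans to watch for floor and ceiling effects at each spatial frequency, but nothing says it will be common. If 5% means sessions or participants, 43 or more remain, at or above 42.

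**Conclusion.** The point holds as a mismatch: the primary model named and the missing-data method named do not work together as written, and no step connecting them is given. It rests on the standard one-row-per-person form of the repeated-measures MANOVA.

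The size is uncertain because the unit of the 5% is not stated. The plausible readings leave 43 to 48 of 50; the worst case, which requires independent loss of single values, leaves about 15 in Study 1. The firmest figure comes from the plan's own attrition: about 40 complete people against 42 required, if attrition reaches 20% and every dropout lacks at least one session. A likelihood analysis would not turn dropouts into completers, but it would use what they contributed.

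**What to change.** Make the primary analysis a linear mixed model, fitted by (restricted) maximum likelihood to every recorded threshold, with participant as the clustering unit.
- Study 1: condition, spatial frequency and condition × frequency.
- Trivector: condition, direction and condition × direction.
- Ellipse 1: a separate model for each parameter, with condition as the factor.

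Prespecify a structured within-person covariance. An unstructured 24 × 24 matrix in Study 1 has 24 × 25 / 2 = 300 parameters and is not feasible with 50 people. The SPSS mixed-model procedure can fit such a model. Keep the complete-case MANOVA as the sensitivity analysis that the run without missing data already implies, and state what the 5% counts.

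The cost is a few sentences in the Statistical Analysis section. The one real downside is that the covariance structure must be chosen in advance and a simple one may be misspecified. If the authors prefer to keep the MANOVA as primary, they would have to name the maximum likelihood step that feeds it and say how the uncertainty of filled values is carried into the test.

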One needs to be careful when interpreting the outcomes of these two experiments because the nicotine may not have been at the peak concentration within the system. Varghese et al. (2011) tested individuals after 30 min of nicotine exposure. As reported by Russell et al. (1976), the peak occurs between 15 and 40 min, after the beginning of the chewing. Thus, conducting an experiment after 30 min of nicotine gum administration could be outside the peak concentration. Naser et al. (2011) did not report the time window. Other limitations include their sample sizes were small, and neither experiment used a blind, controlled design.

The two studies on nicotine and vision suggest that nicotine could enhance photopic vision; however, studies on smoking suggest that nicotine, or another component in tobacco smoke, could impair photopic visual processes slightly by decreasing the pupil size and thereby reducing retinal illumination (Kunchulia et al., 2014; Erdem et al., 2015).

The Effects of Nicotine Gum on Vision Administration (ENIGMA-Vis) is, to the best of our knowledge, the first randomized controlled clinical trial that aims to develop a framework to investigate the effects of nicotine gum on basic visual processing. Here, we discuss the rationale, methods, and design of our ongoing trial. The main aim is to test if individuals have improvements in early-stage visual processing from nicotine gum administration (Levin, 2001). The primary hypothesis guiding our trial is that individuals using higher doses of nicotine gum will show better visual processing. The secondary hypotheses are that (a) differences in visual performance are mediated by the body mass index (BMI), sex (e.g., metabolism for nicotine is different between males and females) but not for other demographic data (e.g., age); and (b) differences in visual performance are mediated by the serum cotinine concentration.

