## Methods and Analysis

### Aims

#### Study 1—Contrast Sensitivity Function

The first study will not be conducted simultaneously with the second study because it is a within-subject, and we cannot exclude the possibility of desensitization among individuals; therefore the participants enrolled in this first study will not participate in the second study. The primary aims for the contrast sensitivity function (CSF) measurements are investigating whether any of three conditions (placebo, 2-mg, or 4-mg doses) (a) influence visual performance for low, middle, and high spatial frequencies (ranging from 0.2 to 20 cycles per degree); (b) whether there is a dose dependency on contrast sensitivity; (c) whether BMI (we intend to select a pool of individuals with different BMIs) influence the results; (d) if there are differences related to sex; and (e) whether there is a serum cotinine concentration dependency of contrast sensitivity. Exploratory aims will test effects by age, height, weight, and years of education.

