### Baseline Measures

All of the baseline measures will be assessed in the allocation phase (see Table 1) at the laboratory. The baseline measures of the participants will include age, sex, height, weight, BMI ($\text{BMI}=\,\frac{\text{Weight}}{{\text{Height}}^{2}}$), and serum cotinine levels. Also, for female participants, information about the menstrual cycle and pregnancy will be assessed. Serum cotinine samples will be collected as a screening to avoid previous nicotine use (biological markers) using 10 ng/ml as a cutoff (Duque et al., 2017). The serum sample will be taken randomly selecting (or selected in order to ensure a balanced representation of gender and BMI) ≥ 50 participants and stored at or below −20°C. They will be measured using a microplate enzyme immunoassay kit, according to the manufacturer’s instruction. Serum cotinine will also be used as secondary outcomes (see “Outcome Measures” section).

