**FIGURE 2 F2:**
[figure not shown]
Illustration of the procedure used in the randomized clinical trial. The black square symbol represents the testing procedure (i.e., task). A washout period of one week between periods will be used.

After 5 min of chewing, the participants will dark-adapt for 10 min. Next, they will be light-adapt to the corresponding display for 3 min. During these 3 min, they will be familiarized with the corresponding test using suprathreshold stimuli. This procedure will ensure that all the participants are in the same photopic adaptation state and understand the instructions. When the testing begins, 18 min will have passed since they started chewing the gum, and they will dispose of the gum.

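### Hypothesis (a) and the analysis text treat BMI, sex and age as mediators of the gum effect, but as fixed baseline traits they can only moderate it

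*Protocol article*

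**What the plan says.** The Introduction states secondary hypothesis (a) as "differences in visual performance are mediated by the body mass index (BMI), sex", with the qualification "but not for other demographic data (e.g., age". Hypothesis (b) uses the same verb for serum cotinine.

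BMI and sex appear among the listed aims of both studies. For Study 1 the BMI aim is "whether BMI (we intend to select a pool of individuals with different BMIs) influence the results".

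Additional Analyses makes three statements that bear on this:
- An exploratory analysis will ask whether sex, age and level of education predict response, and a multivariate regression will ask whether demographics predict the gum's effects.
- A separate regression will be run for cotinine.
- "These variables can be also used as mediators of the interaction between conditions".

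On the design, the Study 1 analysis has "one independent, within-subject variable (condition ∼ three levels", and Study 2 uses the same within-subject factor. On timing, "All of the baseline measures will be assessed in the allocation phase", and "The baseline measures of the participants will include age, sex, height, weight, BMI". Table 1 puts these traits, with education, at week 0 only. Outcome Measures, in contrast, has cotinine measured after each session.

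**The concern.** Mediation asks whether the treatment changes an intermediate variable, which in turn changes the outcome. Gum taken in one of three weekly sessions cannot change a sex, age, schooling or BMI recorded at week 0. The question behind hypothesis (a) is whether the gum effect differs between people with different BMI or between men and women. That is moderation, and the rationale given in the Introduction (nicotine metabolism differing by sex) is a moderation argument.

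The choice of word matters because hypothesis (a) predicts a role for BMI and sex and none for age. A mediation analysis returns nothing for all three. If it were used, the first half of the prediction would appear refuted and the second half confirmed, with neither result depending on the data.

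**Working it through.** The protocol gives no figure to reproduce here. The check is algebraic, with a numerical confirmation.

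**Inputs from the protocol**
- Condition: three levels within person, coded as dose d = 0, 2, 4 mg.
- Trait M (BMI, sex, age or education): one value per person, taken at week 0.
- Session spacing: "A washout period of one week between periods will be used".
- Participants per study (Sample Size): 50 enrolled, at least 42 completing.

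**Condition-to-trait path, within person**

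a = Σ(d_ij − d̄_i)(M_ij − M̄_i) / Σ(d_ij − d̄_i)²

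M_ij = M_i in every session, so M_ij − M̄_i = 0 and the numerator is 0. Each person contributes (−2)² + 0² + 2² = 8 to the denominator, giving 8 × 50 = 400 or 8 × 42 = 336. Hence a = 0/400 = 0, or 0/336 = 0.

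**Same path, all sessions stacked**

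The numerator is Σ_i (M_i − M̄) × Σ_j (d_ij − 2). With complete data the inner sum is −2 + 0 + 2 = 0 for each person, so a = 0 again. Coding condition as categories changes nothing, because mean BMI is the same under placebo, 2 mg and 4 mg.

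**Indirect effect**

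a × b = 0 × b = 0 for any b. If participants are resampled, each brings all three sessions, so a = 0 in every bootstrap resample.

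**Numerical confirmation**

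On invented values for BMI, sex and age, a was 0 (to rounding error) at N = 50 and at N = 42. In one constructed data set of 50 people, the gum effect was made to rise with BMI by 0.05/2 = 0.025 per mg per BMI unit. All 5,000 participant-level bootstrap values of a × b were 0. Regressing each person's change per mg (4 mg minus placebo, divided by 4) on BMI gave a slope of 0.028 (p about 0.00001). This illustrates the algebra and does not measure lost power.

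**What moderation could detect**

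For an assumed correlation r between BMI and a person's gum effect, power ≈ Φ(atanh(r)·√(n − 3) − z). At n = 42 and r = 0.4, atanh(0.4)·√39 = 0.424 × 6.245 = 2.646.
- Two-sided 0.05: Φ(2.646 − 1.960) = 75%.
- Two-sided 0.01, the level in Sample Size: Φ(2.646 − 2.576) = 53%.

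| n | two-sided alpha | r = 0.3 | r = 0.4 | r = 0.5 |
|---|---|---|---|---|
| 42 | 0.05 | 49% | 75% | 93% |
| 42 | 0.01 | 26% | 53% | 80% |
| 50 | 0.05 | 56% | 83% | 97% |
| 50 | 0.01 | 33% | 63% | 88% |

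The correlations are assumptions; the protocol gives none. The zero indirect effect does not depend on them.

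**The case against.** The strongest reply is that the protocol already contains the right analysis. Additional Analyses commits to a regression of the gum's effects on demographics, which is moderation in substance. The mediator use is only permitted as an extra. A reader might infer that hypothesis (a) cannot be tested in this trial, or that its answer is settled before data collection. The documents support neither inference, because both would require the investigators to drop the committed regression and run only the optional mediation. For the same reason, the zero from a mediation analysis is not a measure of power that the trial will lose.

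Other parts of the reply also have weight:
- The mediator sentence directly follows the one on cotinine, which is measured after each session and can be a mediator. The sentence is therefore not wrong for every variable it may cover.
- BMI may be meant under demographics, since the Introduction names BMI and sex and then refers to other demographic data. However, the abstract and Outcome Measures list BMI separately from demographics, so the point stays unclear.
- The only bootstrap in the protocol (5,000 resamples, Study 2 analysis) concerns the colour-test parameters, not these traits.
- Dropout could make the stacked-session path non-zero, but only as an artefact of missing rows. The within-person path stays at 0, and the protocol expects at most 5% missing data.

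The reply does not rescue the mediator wording. Hypothesis (a) is written for the one analysis that cannot inform it. Hypothesis (b) uses the same word where mediation is possible, so a reader cannot tell that (a) means something else.

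**Conclusion.** The protocol is wrong as written, with limited consequences. For BMI, sex, age and education a mediation analysis gives an indirect effect of exactly 0 whatever the data. This rests on two features of the design: the traits are recorded once before any gum, and condition varies within person. In stacked form it also needs complete data.

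Hypothesis (a) remains testable as moderation, and a regression that can do this is already planned, clearly so for sex and age. What remains is a hypothesis worded for an uninformative analysis, an optional analysis that would mislead if reported, and doubt whether BMI, an aim of both studies, is in the planned regression.

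**What to change.** - **Introduction, hypothesis (a):** state that the gum effect is moderated by BMI and sex, and is not expected to vary with other demographics such as age.
- **Additional Analyses:** replace the mediator sentence by moderation for BMI, sex, age and education. Either test condition × BMI and condition × sex in the within-subject model, or regress each person's active-minus-placebo change on these traits. Name BMI explicitly beside sex, age and education.
- **Cotinine:** restrict the word mediator, and any mediation analysis, to the post-session level.

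The cost is the wording of one hypothesis and a few analysis sentences. All the traits are already collected at week 0, so no new data or visits are needed.
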